### Secondary endpoints: immunogenicity read-outs

We used descriptive statistics (medians and IQR) to describe all pre-defined immunogenicity readouts at each study time point. In the IgG assay, we also described the number and proportion of vaccine seroconverters in each group defined as an increase in H56 IgG-responses of  $>2$ -fold from day 84 to any time point after.

Immunogenicity read-outs of primary priority for Hypothesis 1 were responses to treatment defined as the change from day 0 to day 84 in the defined outcomes (**Table 3**). The outcomes were analyzed using median regression with treatment as only independent explanatory factor. The treatment difference of the combination of both groups allocated to etoricoxib (etoricoxib-group and etoricoxib+H56:IC31-group) and the combination of controls and the H56-IC31-group (vaccine not administered until day 84) were calculated as estimated difference in median response with 95% confidence interval based on 1000 bootstrap replications and corresponding two-sided p-value. For Hypothesis 2 and Hypothesis 3, immunogenicity read-outs of primary priority were responses to vaccine treatment defined as the change from day 84 to day 154 (**Table 4 and 5**). The seed for the bootstrap replications was set to 20200316 (pre-defined as the date of the final statistical analysis plan (Version 1.0)).

Exploratory post-hoc analyses were performed for immunogenicity readouts predefined as secondary and tertiary priority from day 84 to day 154 using the same statistical analyses as for the primary priority read-outs described above.

Data were collected in the eCRF Viedoc™ version 4.66.7823.20827 and Microsoft Excel 2016. Statistical analyses were performed in STATA version 16 (StataCorp) and figures drawn in GraphPad Prism version 7.02.

## Etoricoxib concentration

The analysis of plasma concentrations of Etoricoxib in human plasma has been performed using LC-MS/MS and samples were analyzed by Vitas AS, Oslo. 300 µL of human plasma was precipitated with 900 µL isopropanol containing deuterium labeled etoricoxib internal standard. After thorough mixing (10 min) and centrifugation (10 min, 4000 g at 10°C), an aliquot of 5 µL was injected from the supernatant into the High Performance Liquid Chromatography (HPLC) system. HPLC was performed with an Agilent 1260 liquid chromatograph (Agilent Technologies, Palo Alta, CA, USA) interfaced by atmospheric pressure chemical ionization (APCI) to a 6460 Agilent Technologies mass spectrometric detector. Etoricoxib was separated on a Kinetex C18, 100A, 2.6 µm column (Phenomenex, Torrance CA, USA). The column temperature was 50 °C. An eight-point calibration curve prepared in plasma covering concentrations from 0.17 to 4.0 µg/ml was used. The LOD for the method is 0.01 µg/ml and LOQ is 0.05 µg/ml.

[figure not shown]

**Supplementary Figure 1:** 24 hour concentration profile of etoricoxib after daily intake etoricoxib 120 mg x1. Plasma taken from patients (N=5) randomized to study group with etoricoxib alone. Measurements taken approximately 7 days after start of etoricoxib treatment to ensure steady state.

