The anti-TB drug rifampicin that is included in the standard regimen for TB patients recruited to this study is a CYP3A inducer in the liver and will thus reduce the serum concentration of COX-2i. Co-administration of 120 mg etoricoxib with daily doses of 600 mg rifampin resulted in a mean 65% decrease in etoricoxib AUC and 40% decrease in Cmax (33). The geometric mean ratios (etoricoxib

with rifampin/etoricoxib alone) for AUC (0-inf) and Cmax in these patients were: AUC: 0.35 (90% CI: (0.31, 0.40)), with a range of 0.25 - 0.50. Cmax: 0.60 (90% CI: (0.43, 0.84) with a range of 0.29 - 0.87). In the same individuals, the ranges of AUC's and Cmax's during rifampin treatment were as follows: AUC (0-inf) (ug\*hr/mL): 2.41-6.42 with a mean of 3.80 and SD of 1.36. Cmax (ng/mL): 362-1616 with a mean of 733 and SD of 394. Tmax for etoricoxib was not significantly altered during rifampin treatment, but the apparent terminal t1/2 (hour) was significantly different (6.8 hours with rifampin versus 14.4 hours without).

Thus, we will use Arcoxia 120 mg, the maximal dose approved (and recommended for acute arthritis urica) to overcome too low serum concentrations when co-administrated with rifampicin in TB patients. However, the serum concentration of rifampicin will not be affected and there are no interactions between COX-2i and any of the three other anti-TB drugs included in the standard regimen (isoniazide, ethambutol, pyrazinamide).

Analysis of serum-concentration of COX-2i is not routinely available and it is thus not possible to use for drug monitoring during the study. However, pharmacokinetic parameters in serum after 7 days of etoricoxib when steady state is expected (33) will be analyzed in study arm #1 in retrospect for research purposes and correlated to tolerance and immunogenicity and before inclusion of study arm #4 to achieve optimal dosing. If intolerable adverse reactions occur to etoricoxib the dose will be reduced to 90 mg or stopped.

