### **7.2.5 Pharmacokinetics**

The AUC and Cmax of etoricoxib at steady state after 7 days of treatment will be analyzed in Arm #1 in order to study the degree of interaction between etoricoxib and rifampicin. Blood samples will be collected in heparinized tubes at regular intervals during 96 hours as previously described (32). The blood samples will be protected from light and stored on ice until the plasma could be separated. The separated plasma was stored at -20°C until analysis for etoricoxib.

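### The etoricoxib assay section claims an LOQ of 0.05 µg/ml but describes a calibration curve starting at 0.17 µg/ml, a gap in which much of the expected dosing interval falls

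*Protocol*

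**What the plan says.** The supplementary section Etoricoxib concentration describes the LC-MS/MS method: "An eight-point calibration curve prepared in plasma covering concentrations from 0.17 to 4.0" µg/ml. The next sentence gives an LOD of 0.01 µg/ml and the quantification limit ("ml and LOQ is 0.05" µg/ml). The figure legend in that section describes a "24 hour concentration profile of etoricoxib after daily intake etoricoxib 120 mg x1" in five patients of the etoricoxib-only arm.

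Section 1.3.4 gives the exposure to expect when etoricoxib 120 mg is taken with rifampin. AUC in µg·h/ml is "2.41-6.42 with a mean of 3.80 and SD of 1.36", Cmax in ng/ml is "362-1616 with a mean of 733 and SD of 394", and terminal half-life is "6.8 hours with rifampin versus 14.4 hours without". It adds that co-administration "resulted in a mean 65% decrease in etoricoxib AUC and 40% decrease in C"max. The same section describes etoricoxib 120 mg as linear, with steady state after 7 days of once-daily dosing.

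Section 7.2.5 sets the use of the assay: "The AUC and Cmax of etoricoxib at steady state after 7 days of treatment will be analyzed in Arm #1", to study the rifampicin interaction. Section 2 lists this as a secondary objective. Section 1.3.4 adds that the results will be correlated with tolerance and immunogenicity. The document does not say how a concentration below 0.17 µg/ml, or below 0.05 µg/ml, enters the AUC.

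**The concern.** A limit of quantification normally has a standard at or below it. Here the two adjacent statements do not fit together: either a figure is misprinted, or results between 0.05 and 0.17 µg/ml count as quantified with no calibrator beneath them, or there is validation at 0.05 that the text does not mention.

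This would be a footnote if concentrations were expected to stay well above 0.17. They are not. Rifampicin lowers exposure and shortens the half-life, so the later part of each dosing interval should fall in the doubtful band. AUC is one of only two named PK parameters, and it depends on that part. The affected share also grows as exposure falls, so any error would vary with the quantity that is to be correlated with tolerance and immunogenicity.

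**Working it through.** **Inputs.** Lowest calibrator 0.17, top 4.0 and LOQ 0.05 µg/ml come from Etoricoxib concentration. AUC 3.80 (2.41-6.42; SD 1.36) µg·h/ml, Cmax 0.733 (0.362-1.616) µg/ml, half-life 6.8 h, the AUC and Cmax ratios and linearity come from section 1.3.4. The dosing interval is 24 h.

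**1. The plan's own figures.** The geometric mean ratios are 0.35 (AUC) and 0.60 (Cmax). Then 1 − 0.35 = 65% and 1 − 0.60 = 40%, which reproduces the stated decreases.

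**2. The gap.** 0.17/0.05 = 3.4.

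**3. Average concentration.** Under linearity the steady-state AUC over 24 h equals the AUC to infinity, so the average is AUC/24:
- mean: 3.80/24 = 0.158 µg/ml
- lowest AUC: 2.41/24 = 0.100 µg/ml
- highest AUC: 6.42/24 = 0.268 µg/ml

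The average reaches 0.17 at AUC = 0.17 × 24 = 4.08. This step needs no curve shape.

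**4. Share of the interval and of the AUC below 0.17.** This needs a curve shape, which the documents do not give. A simple version puts the peak at time zero and lets two phases decline:

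C(t) = [aα/(1 − e^(−24α))]·e^(−αt) + [bλ/(1 − e^(−24λ))]·e^(−λt), with a + b = AUC, C(0) = Cmax and λ = ln 2/6.8 = 0.1019 per h.

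Mean patient, assumed fast rate α = 0.5 per h:
- 1 − e^(−24λ) = 0.913, so 0.500a + 0.1116b = 0.733 with a + b = 3.80. This gives a = 0.795 and b = 3.005.
- C(t) = 0.398·e^(−0.5t) + 0.335·e^(−0.1019t).
- C falls to 0.17 at 7.3 h, leaving 16.7 h below it. The area after that point is 1.30, and 1.30/3.80 = 34%.
- C falls to 0.05 at 18.7 h. The area after that point is 0.206, and 0.206/3.80 = 5.4%.

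With α = 0.3 per h the results are again 16.7 h below 0.17, with 29% of the AUC below 0.17 and 6.8% below 0.05. Adding an absorption phase (peak at 1-2 h) and varying the share carried by the terminal phase widens the ranges:

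| Case | Average, µg/ml | AUC share below 0.17 | AUC share below 0.05 |
|---|---|---|---|
| Mean AUC and Cmax | 0.158 | about 17-36% | about 5-8% |
| Lowest AUC with lowest Cmax | 0.100 | about 40-60% | about 10-13% |
| Highest AUC with highest Cmax | 0.268 | about 10-20% | up to about 5% |

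Time below 0.17 for the mean patient stays near 17 of 24 h.

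**5. Cmax.** The expected range 0.362-1.616 lies wholly inside 0.17-4.0.

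**6. What it could do to the interaction estimate.** Suppose values below 0.17 were dropped and the comparator without rifampicin were measured in full. A true ratio of 0.35 would then read between 0.35 × 5/6 = 0.29 and 0.35 × 2/3 = 0.23, that is, a 71-77% decrease instead of 65%.

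**The case against.** The strongest reply is that the text does not show which figure is wrong. If 0.05 was validated separately, or if 0.17 is a misprint, the loss is only about 5-8% of the mean patient's AUC. That stands, and it is why the first step is to reconcile the figures.

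Other parts of the reply also stand:
- The average of 0.158 is only about 7% below 0.17 (0.012/0.17), and at the top of the AUC range the average is above it.
- The area shares rest on assumed curve shapes and on pairing the lowest AUC with the lowest Cmax and the highest with the highest, which section 1.3.4 does not do.
- The exposure figures come from a cited interaction study at 600 mg rifampin, while section 5.6 gives 450-600 mg by weight.
- PK is a secondary, retrospective research measure, shown for five patients.

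A reader might infer that much of every patient's AUC is unquantifiable. That is true of time but not of area: the share is about a sixth to a third in the mean case and only 10-20% at the highest exposure. A reader might also infer that low values were in fact reported as quantified without support. That cannot be checked, because the concentration figure is not shown and no individual values appear. Nor is a trough or half-life at risk as a planned result, since only AUC and Cmax are named.

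The reply does not remove the inconsistency itself, or the absence of any stated rule for low values.

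**Conclusion.** The point holds as an internal inconsistency with a measurable consequence for one secondary PK parameter. The stated LOQ is 3.4 times below the lowest standard described, and the protocol's own exposure figures put the mean steady-state average (0.158 µg/ml) and about 17 of 24 h in or below that gap. If 0.17 is the true floor, about one sixth to one third of the mean patient's AUC is uncalibrated, with about 10-20% at the highest exposure and 40-60% at the lowest. If 0.05 is valid, the mean-case loss is about 5-8%.

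The 3.4 is read straight from the text, and the average needs only the quoted AUC and linearity. The time and area shares also need an assumed curve shape. Cmax is unaffected. The documents do not support the stronger conclusion that the AUC results are invalid or that the samples must be re-assayed.

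**What to change.** Reconcile the two figures in Etoricoxib concentration:
- If either is a misprint, correct it.
- If the method was validated at 0.05 µg/ml, cite that validation and describe the standard or quality-control samples used there.
- Otherwise, restate the lower limit of quantification as 0.17 µg/ml. Report the 24 h AUC twice, once with values below 0.17 set to zero and once with them as measured or extrapolated, and carry that range into the rifampicin interaction estimate and any correlation with tolerance or immunogenicity.

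In every case, add a sentence on how values below the limit enter the AUC. The cost is a less favourable stated LOQ and one sensitivity calculation in five profiles. Re-running retained plasma with lower standards, if any remains, would settle the matter more fully but is optional.

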**Supplementary Table 7. Baseline characteristics by study arm for the Full analysis Set (FAS), N=40**

|                                               | Etoricoxib (N =10) | H56:IC31(N = 12)  | Controls(N = 10)  | Etoricoxib + H56:IC31 (N = 8) |
|-----------------------------------------------|--------------------|-------------------|-------------------|-------------------------------|
| Demography                             |                    |                   |                   |                               |
| Sex (Male)                                    | 5 (50%)            | 8 (67%)           | 4 (40%)           | 4 (50%)                       |
| Age (years), Median (Q1, Q3)                  | 31·0 (23·0, 35·0)  | 24·0 (20·5, 26·5) | 28·0 (23·0, 34·0) | 28·0 (24·5, 36·0)             |
| Ethnicity                                     |                    |                   |                   |                               |
| Asian                                         | 2 (20%)            | 2 (17%)           | 4 (40%)           | 3 (38%)                       |
| Black                                         | 5 (50%)            | 7 (58%)           | 6 (60%)           | 3 (38%)                       |
| Caucasian                                     | 1 (10%)            | 3 (25%)           | 0 (0%)            | 2 (25%)                       |
| Other                                         | 2 (20%)            | 0 (0%)            | 0 (0%)            | 0 (0%)                        |
| TB related medical history             |                    |                   |                   |                               |
| BCG scar                                      |                    |                   |                   |                               |
| Yes                                           | 2 (20%)            | 5 (42%)           | 4 (40%)           | 6 (75%)                       |
| No                                            | 7 (70%)            | 6 (50%)           | 6 (60%)           | 1 (13%)                       |
| Unknown                                       | 1 (10%)            | 1 (8%)            | 0 (0%)            | 1 (13%)                       |
| Previous TB treatment                         | 0 (0%)             | 1 (8%)            | 2 (20%)           | 1 (13%)                       |
| Co-morbidity and Risk factors          |                    |                   |                   |                               |
| Allergy                                       | 2 (20%)            | 1 (8%)            | 3 (30%)           | 2 (25%)                       |
| Previous gastric ulcer/gastroenteric bleeding | 0 (0%)             | 1 (8%)            | 1 (10%)           | 0 (0%)                        |
| Liver disease/failure                         | 1 (10%)            | 0 (0%)            | 1 (10%)           | 0 (0%)                        |
| Pulmonary disease                             | 0 (0%)             | 0 (0%)            | 0 (0%)            | 0 (0%)                        |
| Other medical condition*                      | 2 (20%)            | 3 (25%)           | 3 (30%)           | 4 (50%)                       |
| Smoking status                                | 2 (20%)            | 0 (0%)            | 0 (0%)            | 1 (13%)                       |
| Alcohol use >3 units/week                     | 2 (20%)            | 1 (8%)            | 1 (10%)           | 3 (38%)                       |
| Drug abuse                                    | 0 (0%)             | 1 (8%)            | 0 (0%)            | 0 (0%)                        |
| Clinical Classification and Radiology  |                    |                   |                   |                               |
| TB diagnosis                                  | 8 (80%)            | 10 (83%)          | 7 (70%)           | 4 (50%)                       |
| Pulmonary                                     | 1 (10%)            | 2 (17%)           | 0 (0%)            | 1 (13%)                       |
| Pulmonary/extrapulmonary                      | 1 (10%)            | 0 (0%)            | 3 (30%)           | 3 (38%)                       |
| Extrapulmonary                                |                    |                   |                   |                               |
| Lymph nodes / lymphadenitis                   | 1                  | 1                 | 3                 | 4                             |
| Bones, joint and soft tissue                  | 0                  | 0                 | 0                 | 1                             |
| Other                                         | 1                  | 1                 | 0                 | 0                             |
| Radiology                                     |                    |                   |                   |                               |
| Pulmonary cases                               |                    |                   |                   |                               |
| Infiltrate                                    | 7                  | 11                | 3                 | 3                             |
| Cavity                                        | 5                  | 3                 | 1                 | 0                             |
| Pleural fluid                                 | 1                  | 1                 | 0                 | 0                             |
| With hilary/mediastinal changes               | 0                  | 2                 | 0                 | 0                             |
| Clinical Features                      |                    |                   |                   |                               |
| Symptoms (cough, chest pain, night sweat)     |                    |                   |                   |                               |
| No symptoms                                   | 2 (20%)            | 2 (17%)           | 7 (70%)           | 5 (63%)                       |
| 1 symptom                                     | 1 (10%)            | 1 (8%)            | 1 (10%)           | 2 (25%)                       |
| ≥2 symptoms                                   | 7 (70%)            | 9 (75%)           | 2 (20%)           | 1 (13%)                       |
| BMI** (kg/m2) Median (Q1, Q3)                 | 20·4 (18·9, 21·6)  | 20·8 (19·1, 21·7) | 21·7 (18·9, 24·9) | 21·6 (18·1, 23·8)             |
| Body temperature (°C) Median (Q1, Q3)         | 36·6 (36·5, 37·1)  | 36·3 (36·1, 36·8) | 36·6 (36·4, 37·0) | 36·5 (36·2, 36·6)             |
| Laboratory data                        |                    |                   |                   |                               |
| Haemoglobin (g/dl)                            |                    |                   |                   |                               |
| Median (Q1, Q3)                               | 13·3 (12·6, 14·9)  | 13·3 (12·3, 14·9) | 13·9 (13·4, 15·1) | 14·0 (13·3, 15·0)             |
| N (% Non-missing)                             | 9 (90%)            | 10 (83%)          | 8 (80%)           | 8 (100%)                      |
| Sedimentation rate (mm)                       |                    |                   |                   |                               |
| Median (Q1, Q3)                               | 34·0 (13·0, 76·0)  | 20·0 (11·0, 52·0) | 13·0 (5·0, 35·0)  | 26·0 (15·0, 41·0)             |
| N (% Non-missing)                             | 9 (90%)            | 10 (83%)          | 9 (90%)           | 7 (88%)                       |
| C-reactive protein (mg/L)                     |                    |                   |                   |                               |
| Median (Q1, Q3)                               | 19·6 (0·6, 52·2)   | 7·2 (0·7, 36·5)   | 0·7 (0·0, 6·4)    | 2·8 (0·9, 7·8)                |
| N (% Non-missing)                             | 10 (100%)          | 11 (92%)          | 9 (90%)           | 7 (88%)                       |
| Quantiferon result                            |                    |                   |                   |                               |
| Negative                                      | 0 (0%)             | 0 (0%)            | 1 (10%)           | 0 (0%)                        |
| Positive                                      | 9 (90%)            | 10 (91%)          | 8 (80%)           | 8 (100%)                      |
| Indeterminate                                 | 1 (10%)            | 1 (9%)            | 1 (10%)           | 0 (0%)                        |
| Median IU/ml (Q1, Q3)                         | 4·0 (3·7, 7·2)     | 4·8 (2·0, 8·0)    | 6·4 (3·9, 11·3)   | 12·6 (3·6, 15·4)              |
| N (% Non-missing)                             | 9 (90%)            | 10 (83%)          | 8 (80%)           | 8 (100%)                      |

Unless indicated in table, no values were missing. \*No participants had diabetes. \*\*BMI: Body Mass index

## Supplementary Table 8. Follow-up time, study discontinuation and adherence

### Follow-up time and study discontinuation all arms - Safety Analysis Set\* (N=47)

|                                                                  | Etoricoxib
(N = 13) | H56:IC31
(N = 12) | Controls
(N = 12) | Etoricoxib +
H56:IC31
(N = 10) |
|------------------------------------------------------------------|------------------------|----------------------|----------------------|--------------------------------------|
| Follow-up time in days                                    |                        |                      |                      |                                      |
| Mean (SD)                                                        | 200.4 (83.0)           | 227.3 (44.4)         | 214.0 (84.1)         | 199.8 (93.6)                         |
| Min, Max                                                         | 11.0, 265.0            | 88.0, 250.0          | 50.0, 330.0          | 20.0, 285.0                          |
| Did the subject complete the study                        |                        |                      |                      |                                      |
| Yes                                                              | 9 (69%)                | 10 (83%)             | 9 (75%)              | 6 (60%)                              |
| No                                                               | 4 (31%)                | 2 (17%)              | 3 (25%)              | 4 (40%)                              |
| Reasons for study discontinuation                         |                        |                      |                      |                                      |
| Voluntary discontinuation by the subject                         | 0 (0%)                 | 1 (50%)              | 0 (0%)               | 0 (0%)                               |
| Safety reason as judged by the Principal Investigator            | 1 (25%)                | 0 (0%)               | 0 (0%)               | 2 (50%)                              |
| Major protocol deviation                                         | 1 (25%)                | 0 (0%)               | 0 (0%)               | 0 (0%)                               |
| Pregnancy during follow-up                                       | 0 (0%)                 | 0 (0%)               | 2 (67%)              | 1 (25%)                              |
| TB disease progression                                           | 1 (25%)                | 0 (0%)               | 0 (0%)               | 0 (0%)                               |
| Autoimmune disease or immunosuppressive therapy during follow-up | 0 (0%)                 | 0 (0%)               | 1 (33%)              | 0 (0%)                               |
| Moved abroad                                                     | 1 (25%)                | 1 (50%)              | 0 (0%)               | 1 (25%)                              |

\*Safety analysis set defined as patients that received at least one dose of etoricoxib and/or one dose of H56:IC31

